**Methods/Design:**

The STAR trial is an NIHR HTA-funded UK pragmatic randomised phase II/III clinical trial in the first-line treatment of advanced RCC. Participants will be randomised (1:1) to either a sunitinib CCS or a DFIS. The overall aim of the trial is to determine whether a DFIS is non-inferior, in terms of 2-year overall survival (OS) and quality adjusted life years (QALY) (averaged over treatment and follow up), compared to a CCS. The QALY primary endpoint was selected to assess whether any detriment in terms of OS could be balanced with improvements in quality of life (QoL). This is a complex trial with a number of design challenges, and to address these issues a feasibility stage is incorporated into the trial design. Predetermined recruitment (stage A) and efficacy (stage B) intermediary endpoints must be met to allow continuation to the overall phase III trial (stage C). An integral qualitative patient preference and understanding study will occur alongside the feasibility stage to investigate patients’ feelings regarding participation or non-participation in the trial.

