#### Overall primary objectives

• To determine whether a sunitinib DFIS is non-inferior in terms of 2-year OS and quality-adjusted life years (QALYs) (averaged over trial recruitment and follow-up) compared to a sunitinib CCS, in patients with locally advanced and/or metastatic clear cell RCC.

Oncological treatments for patients with incurable disease require assessment using standard measures of efficacy, such as survival. It is however recognised that other measures must also be taken into consideration including QoL and cost, particularly in the context of the economic constraints of the NHS. When seeking approval from NICE for a new treatment, all of these outcomes are considered. A composite co-primary endpoint (QALY averaged over trial recruitment and follow up) was selected as a primary outcome measure to more accurately assess whether any detriment in survival could be balanced with improvements in QoL and cost-effectiveness. Limitations of the previously reported QoL data relating to advanced RCC means significant uncertainty remains about the profile, timing and magnitude of the QoL impact of sunitinib treatment, hence OS has been retained as a co-primary endpoint.

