#### Stage specific primary objectives

*Stage A:* To establish the feasibility of performing the phase III trial in terms of average recruitment between months 10–21 (inclusive). This is to ensure that sufficient participants can be recruited to enable its completion in a timely manner, assuming continuation to stage C.

*Stage B***:** To provide initial efficacy data by comparing time to strategy failure^a^ (TSF) in both arms and test for non-inferiority between the approaches to assess comparability.

*Stage C:* 2 year OS and QALY averaged over study recruitment and follow up

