### Sample size

In total, for all 3 stages, 1000 patients will be required (allowing for a 10% drop-out), 210 in stages A/B (phase II), and a further 790 in stage C (phase III). Stages A/B will be performed in 13 UK sites, and assuming continuation to stage C, then the trial will be opened up to a further 26 sites. The sample size is based on the co-primary endpoints, however it will also be adequate to obtain meaningful conclusions regarding the key secondary endpoints e.g. QoL.

A computer-generated minimisation programme that incorporates a random element will be used to ensure that treatment groups are well balanced for the following factors: Motzer prognostic group
[15] (favourable risk (0 factors) vs. intermediate risk (1–2 factors) vs poor risk (≥ 3 factors)), trial site, sex, age (< 60 years vs. ≥ 60 years), disease status at randomisation (locally advanced vs. metastatic) and whether or not the patient has had a previous nephrectomy.

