### Recruitment

Participant recruitment is planned over 21 months in stages A/B, and then to seamlessly continue for a further 33 months assuming continuation to stage C, with a number of other centres opening to recruitment in stage C. All participants will be followed up until 2 years after the last participant is randomised. The duration of the trial is expected to be 84 months including set up, recruitment, follow-up and analysis. Recruitment commenced in January 2012.

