Information will be collected at clinic visits at baseline, and day 1 of sunitinib cycle 1, 2, 3 and 4. Administration in clinic will enable patients to be supported in their completion, if required, prior to initiation of postal questionnaires. After this timepoint EQ-5D^TM^/EQ-VAS information (a simple 2 page assessment) will be completed every 2 weeks by patients at home, over 18 weeks. At clinical assessment visits the FSKI and FACT-G will continue to be completed 6 weekly. It is the period when CCS arm patients continue treatment and most patients on the DFIS arm stop treatment (i.e. after 6 months), when QoL differences are predicted to be greatest and hence this is when QoL data collection is most intensive. After the intensive collection has finished, collection of all information (including EQ-5D/VAS) will revert to 6 weekly in clinic.

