#### Stage C

There are two co-primary outcome measures: OS and averaged QALY. The two null hypotheses are that DFIS is not inferior to CCS in terms of OS and QALYs. To calculate a sample size for the primary OS endpoint, a difference of ≤7.5% in OS at two years between the two arms has been assumed to be an acceptable non-inferiority margin (equivalent to a hazard ratio of 0.806). To demonstrate this non-inferiority with 80% power will require the recruitment of approximately 1000 patients (allowing for 10% of patients being lost to follow-up). To calculate a sample size for the primary QALY endpoint a difference of ≤10% in mean QALYs between the two arms has been assumed to be an acceptable non-inferiority margin. While it is hoped that survival will be equivalent between the two arms, a slightly poorer survival in the DFIS arm would be acceptable if offset by a significant QoL gain in these patients, this will be captured through the QALY measure. With a hazard ratio of 0.9 in favour of CCS and 1000 patients recruited, simulations give a power of 84% to show non-inferiority in the QALY endpoint. Both non-inferiority sample sizes are calculated assuming a 1-sided 97.5% confidence interval, as described by Kay
[26], and assuming patients are recruited in total over 4.5 years, with a further follow-up of 2 years before evaluating the data.

For Stage B TSF and Stage C OS endpoints, the primary analysis will comprise Kaplan-Meier curves including those adjusted for the minimisation factors
[27], giving 95% CIs for the TSF and 2-year survival difference. A a Cox proportional hazards model analysis adjusting for minimisation factors and associated hazard ratios plus 95% CIs for the DFIS vs. CCS comparisons will be pesented, as appropriate for the non-inferiority analysis. The analysis of primacy is the Cox model.

For the QALY endpoint mean differences in QALYs, calculated via the EQ-5D, between the arms, with 95% confidence limits, will be calculated. Multivariate linear regression will be used to adjust for minimisation factors. If the data are not normally distributed, transformations to normality will be investigated. If no such transformations can be found we will analyse the difference between median QALYs and we will calculate confidence intervals for the differences between these medians as described by Campbell and Gardner
[28].

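### The co-primary QALY regression adjusts for the minimisation factors only and leaves out baseline EQ-5D utility, which the trial collects; adding it is a free gain in precision

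*Protocol article*

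**What the plan says.** Stage C gives the co-primary QALY analysis in two steps. First: "For the QALY endpoint mean differences in QALYs, calculated via the EQ-5D, between the arms, with 95% confidence limits, will be calculated". Then: "Multivariate linear regression will be used to adjust for minimisation factors". If the data are not normal, a transformation is tried, and failing that a difference in medians.

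The minimisation factors are listed under Sample size: Motzer group, site, sex, age, and finally "disease status at randomisation (locally advanced vs. metastatic) and whether or not the patient has had a previous nephrectomy". No utility or quality-of-life score is among them.

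The Quality of life section shows that the measurement exists: "Information will be collected at clinic visits at baseline, and day 1 of sunitinib cycle 1, 2, 3 and 4".

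The QALY period is worded in two ways. The Methods/Design part of the abstract has "averaged over treatment and follow up". The overall primary objective has "averaged over trial recruitment and follow-up", and the Stage C objective has "2 year OS and QALY averaged over study recruitment and follow up". On follow-up, the Recruitment section says: "All participants will be followed up until 2 years after the last participant is randomised".

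**The concern.** A QALY is the area under a participant's utility curve, and that curve starts at the baseline utility. People who start high tend to accrue more QALYs for the same survival, so baseline EQ-5D should predict the outcome directly. The minimisation factors may relate to survival but do not measure utility. Leaving baseline EQ-5D out keeps this predictable variation in the residual, and any chance difference between arms at baseline passes into the estimated difference. At stake is the width of the confidence interval that is set against the 10% margin in a co-primary non-inferiority test.

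This is more than a detail left to a later document. The article names the covariate set, and an analysis plan that follows it would repeat that set.

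**Working it through.** **Inputs from the protocol article.** 1000 participants less 10% loss, 1:1, so 1000 × 0.9 / 2 = 450 per arm. 210 participants are recruited in the first 21 months and 790 in the next 33. QALY margin 10%, one-sided 2.5%. Median OS on sunitinib 26.4 months (Background). Utility 0.6-0.8 in stable disease (Health economics).

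**Assumed, because not given.** Mean utility 0.7, between-person SD 0.15-0.25, measurement noise SD at baseline 0.10-0.15, constant utility capped at 1, exponential survival, equal arms, baseline utility unrelated to survival.

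1. *The plan's own figures.* The OS sample size reproduces. Events = 4(1.960 + 0.842)² / (ln 0.806)² = 675. With 54 months of uniform accrual plus 24 months, the event probabilities are 0.715 and 0.785, mean 0.750. Then 675 / 0.750 = 900, and 900 / 0.9 = 1000. The 84% QALY power cannot be reproduced, because the utility SD and the utility gain behind it are not stated.

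2. *Potential follow-up.* Recruitment lasts 21 + 33 = 54 months. The last participant has 24 months and the first 54 + 24 = 78.

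3. *Variance explained.* Let Q = U·X, with U the person's utility and X the years alive within follow-up, and let measured baseline be B = U + noise. With U independent of X:
   - R² = (E[X]·σ_U²)² / [(σ_U² + σ_e²)·Var Q], where Var Q = (σ_U² + μ²)(σ_X² + E[X]²) − μ²E[X]².
   - Simulation with 21% of entrants having 57-78 months and 79% having 24-57 months gives E[X] = 2.17 and σ_X = 1.45 years.
   - Low end (σ_U = 0.15, σ_e = 0.15): (2.17 × 0.0225)² = 0.00238; Var Q = 0.5125 × 6.811 − 2.307 = 1.18; R² = 0.00238 / (0.045 × 1.18) = 4.5%.
   - High end (σ_U = 0.25, σ_e = 0.10): (2.17 × 0.0625)² = 0.0184; Var Q = 0.5525 × 6.811 − 2.307 = 1.46; R² = 0.0184 / (0.0725 × 1.46) = 17%.
   - The formula ignores the cap. Capping utility at 1 in the simulation gives 4.2% and 15%. Hence about 4-15%.

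4. *Power under those assumptions.* Power = Φ(0.10 × mean / (SD × √(1 − R²) × √(2/450)) − 1.96).
   - Low end (mean 1.515, SD 1.084): 55.4% without baseline EQ-5D, 57.2% with it.
   - SD 0.25 (mean 1.487, SD 1.157): 48.7% without; 54.5% with noise 0.125 and 55.2% with noise 0.10.
   - The gain is roughly 2-6 points. Only the gain is of interest. The starting levels assume no utility benefit of the drug-free strategy and are not comparable with 84%.

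5. *Other assumptions, starting from 84%.* Here the hazard ratio is 0.9, utility 0.6-0.8, SD 0.20-0.25, follow-up uniform over 24-78 months, and the utility gain is set to return 84%. If baseline EQ-5D correlates 0.3-0.7 with later utility but not with survival, it removes 1-7% of the variance. If it also predicts survival (log-hazard 0.2-0.4 per SD), it removes 8-25%. Since 84% corresponds to 0.994 + 1.960 = 2.954, power becomes Φ(2.954/√(1 − R²) − 1.96): 84.4% at R² = 1%, 86.5% at 7%, 86.9% at 8% and 92.7% at 25%.

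6. *Period wording.* Treatment and recruitment are different spans, so the abstract and the two objectives do not describe the same averaging period.

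**The case against.** The strongest reply is that the omission harms nothing that was promised. In a randomised trial a chance baseline imbalance is already covered by the standard error, so the unadjusted estimate is not biased. The 84% was computed for the planned schedule of 4.5 years of recruitment plus 2 years, and an interim utility analysis is planned to revisit QALY power. All of this stands. It limits the size of the point, but it gives no reason to leave out a predictor that is already collected.

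Three stronger readings are tempting, and the document does not support them.

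- *That censored QALYs will be analysed as complete, or losses as deaths.* The article says nothing on this and defers to a full analysis plan. What can be said is that a mean difference, a linear regression and a median difference do not by themselves handle censoring.
- *That unequal follow-up is a major loss of precision.* Potential follow-up explains only about 4-6% of QALY variance, and its distribution is the same in both arms by randomisation. With constant utility 0.7, equal arms and 450 per arm, power is 91% at a common 24 months, 68% at a common 46 months (about the mean follow-up) and 61% at 24-78 months. So 91 − 68 = 23 of the 30 points come from shortening the horizon and only 7 from variability.
- *That the QALY should be cut at 24 months.* That is a different estimand with a different mean under the 10% margin. It drops later survival and quality of life, which the declared endpoint is meant to weigh. Baseline EQ-5D would explain more of a 24-month QALY (about 8-27%), but that is not the planned endpoint.

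**Conclusion.** The point holds as an available improvement to a co-primary analysis. The named covariates exclude baseline EQ-5D, which is collected and should predict the outcome. Under the first set of assumptions it explains about 4-15% of the variance of the planned QALY, roughly 2-6 points of power. The wider range runs from 1% to 25%, the upper part requiring that baseline utility also predicts survival. Every one of these figures rests on utility values that the article does not give.

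The size is modest. A reader might infer that the trial is underpowered for QALYs or that the estimate is biased; neither follows. The inconsistent wording of the period is real but minor. The unstated horizon and censoring method matter for what is being estimated, and the analysis plan is the place to settle them.

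**What to change.** Add baseline EQ-5D utility as a covariate in the QALY regression alongside the minimisation factors, and say that the baseline questionnaire is the one used.

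Also:
- use one description of the QALY period in the abstract and the objectives;
- state in the analysis plan the time horizon and a censoring-aware method for QALYs, such as inverse-probability weighting or an interval-partitioned estimator.

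The cost is wording only: no new data, no change to the sample size, and one further term in a model with about 900 evaluable participants. The change should be fixed before any comparison of utility by arm, including the planned interim utility analysis. A common 24-month horizon is not required.

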### Trial organisation and administration

The STAR trial is funded by the NIHR Health Technology Assessment programme (Grant ref 09/91/21). The trial is sponsored by the University of Leeds and was developed by the STAR trial management group and medical advisory group, with the support of the UK NCRI Renal Clinical Studies Group. The trial is registered (ISRCTN06473203 EudraCT number 2011-001098-16).

Trial supervision will be established according to the principles of Good Clinical Practice (GCP) and in line with the relevant Research Governance Framework within the UK and through adherence with CTRU standard operating procedures (SOP). The trial will be performed in accordance with the recommendations guiding physicians in biomedical research involving human subjects adopted by the 18th World Medical Assembly, Helsinki, Finland, 1964, amended at the 52nd World Medical Association General Assembly, Edinburgh, Scotland, October 2000. Ethical approval in the UK has been obtained through the National Research Ethics Service (ref 11/NW/0246).

A core Internal Project Team, Trial Management Group (TMG), a Trial Steering Committee (TSC) and DMEC will be established. The independent DMEC will be appointed to review the safety and ethics of the trial, alongside trial progress and the overall direction as overseen by the TSC. Interim reports will be presented to the DMEC, in strict confidence, at, at least, yearly intervals. This committee, in light of the interim data, and of any advice or evidence they wish to request, will advise the TSC if there is proof beyond reasonable doubt that one treatment strategy is better.

### Ancilliary studies

#### Patient preference and understanding study

There is an integral qualitative substudy in two parts which aims to investigate patient’s reasons for entering or declining entry into the STAR trial. The reasons why, and under what conditions, patients participate in clinical trials is an under-researched and poorly understood area, especially in clinical trials in advanced cancer. Nevertheless, the reasons for non-participation are frequently related to how the healthcare professionals involved present the design and objectives of the clinical trial to the patient, and how the patient assimilates this information. It is therefore of importance to understand how patients accept the information about potential participation in a particular clinical trial and what their experiences are of information provision relating to the trial. The perspectives of patients as potential users have become an essential part of determining clinical utility of drugs and/or procedures yet patients’ perspectives on being involved in clinical trials are a severely under-researched area.

It is anticipated that this trial will be complex to discuss with patients, who may have reservations and strong feelings about stopping a treatment that they know to be working. There is only limited guidance from the literature regarding how optimally to present this trial to patients as evidence available will be either too generic, or too specific for the individual trial investigated.

This substudy aims to conduct qualitative semi-structured interviews with up to 50 patients from three clinical research sites with different catchment patterns to increase the diversity of the sample. Twenty-five patients who have declined to participate in the STAR trial and 25 STAR participants randomised to the DFIS arm will be included. The patients who have declined participation will be interviewed to investigate their reasons for declining trial entry. The DFIS participants will be interviewed to investigate their feelings about stopping sunitinib, but also the reasons which led them to initially participate. All interviews will be audio-recorded and professionally transcribed verbatim. The analysis will adopt thematic approach.

Information gained will be utilised to optimise patient information provided relating to the study (audiovisual and PIS) and to inform clinical staff regarding preferred methods of describing the study, which ideally will enable recruitment to be maximised in stage C of the study. Other studies (e.g. the ProtecT study which randomised patients with localised prostate cancer to surgery, radiotherapy or active monitoring) have confirmed the value of such approaches in improving recruitment and taking up of randomisation
[29].

#### Translational studies

Translational research studies are planned to investigate blood and/or tissue markers of sunitinib response and toxicity, and imaging markers to identify earlier evidence of disease response or progression. Imaging sub-studies include an optional CT study and an optional MRI study.

## Discussion

This has been a challenging trial to design, however the design is applicable to many other treatment strategies using different drugs and in different disease areas. Non-standard endpoints were required due to the intermittent nature of the DFIS; as PFS was not an appropriate key intermediary endpoint, TSF was defined and selected. Similar composite endpoints have been used in the previous intermittent chemotherapy CRC trials, and equivalent endpoints in intermittent therapy trials of anti-retrovirals in the treatment of HIV and of antipsychotics in Alzheimer’s disease.

Another issue during design was the use of pazopanib (Votrient^TM^, GSK), another TKI which works via the same mechanism as sunitinib. In the UK it has recently been recommended by NICE as an alternative first-line treatment option for patients with advanced RCC, conditional on pricing. Evidence is awaited regarding the efficacy of pazopanib compared to that of sunitinib in the first-line setting of advanced RCC (the COMPARZ trial). Based on the available evidence when designing the trial sunitinib is currently the only drug permitted for use in stages A/B of the STAR trial. When data becomes available from the COMPARZ trial, a decision will be made as to whether eligibility will be extended to patients treated with pazopanib. If pazopanib is permitted, then an additional minimisation factor will be required, as well as a recalculation of the QALY powering of the trial.

The STAR study will be an important trial. Chemotherapeutic agents have often necessitated restricted periods of treatment due to toxicity, but this is not necessarily true of novel targeted therapies. However, chronic minor side effects such as fatigue can have cumulative major effects on QoL, particularly over longer periods of time. Conflicting pressures exist when establishing a treatment duration, pharmaceutical companies have an interest in prolonged treatment durations, until disease progression or even beyond, but it is usually in the patient’s and healthcare provider’s best interest to use shorter durations of treatment, in terms of toxicity, QoL and cost effectiveness. If successful, the STAR trial design could be easily adapted for use with other systemic anti-cancer therapies in other disease sites. We predict that trial designs such as this will become increasingly utilised in the future, as they allow for incorporation of more complex treatment strategies alongside emphasising the importance of quality as well as quantity of life for patients.

### Endnotes

^a^TSF is defined as the time from randomisation until death; disease progression on sunitinib; disease progression in the DFIS arm during a planned treatment break assuming no further disease response or stabilisation on subsequent sunitinib occurs; participant requires use of a new systemic anti-cancer agent for RCC or significant clinical deterioration where deterioration is assumed to be due to renal cancer progression and not another comorbidity and deterioration sufficient to warrant cessation of sunitinib if on treatment or to preclude restarting sunitinib if on a treatment break on the DFIS arm, without it being clinicially appropriate to arrange radiological confirmation of the progression

^b^SPFI is defined as the sum of the intervals from the start of each treatment block with sunitinib, until radiological evidence of disease progression provided there has been some evidence of disease control prior to ongoing progression

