There is also one randomised phase II study in which 202 patients with metastatic RCC were treated with sorafenib (an alternative TKI). After 12 weeks of sorafenib, the 65 patients with stable disease (SD) were randomly assigned to continue sorafenib (n=32) or placebo (n=33). At 24 weeks 50% of patients continuing sorafenib were progression-free compared with 18% of placebo-treated patients (p=0.0077), however, when sorafenib was re-administered in 28 of the placebo-treated patients with disease progression, further progression was delayed for a median of 24 weeks. The researchers concluded that intermittent treatment with sorafenib resulted in comparable median summative PFS as for those patients receiving continuous sorafenib
[14]. This suggests that patients were not disadvantaged from a brief period of placebo treatment, providing further ethical support for the design of the STAR trial.

At present there is no clearly defined optimal treatment strategy for many targeted therapies, and research in this field is crucial both for patients in terms of QoL and for the National Health Service (NHS) in terms of cost-effectiveness. Regarding sunitinib in advanced RCC, evidence for the cost-effectiveness is currently poor and standard decision criteria did not support its implementation in the NHS. The STAR trial will address the need to gather robust evidence on the costs, QoL and clinical outcomes of sunitinib using both a DFIS and a conventional continuation strategy (CCS). If successful, the design may be applicable to other drugs across a wide range of diseases.

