#### Secondary objectives

The secondary objectives are to evaluate how utilisation of DFIS compared to utilisation of a CCS impacts on: 

• Summative Progression Free Interval (SPFI)^b^

• Time to Strategy Failure (TSF)

• Toxicity (CTCAE v.4.0)

• QoL

• Cost-effectiveness

• Progression free survival (PFS)

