### Intervention

Participants in both arms of the trial will receive sunitinib which will be administered orally at 50 mg once daily on days 1 to 28 of the standard 42 day cycle. Daily doses may be modified for toxicity to 37.5 mg and 25 mg, in line with standard clinical practice.

After completion of at least 4 cycles of sunitinib and maximal radiological response, participants will take up their randomisation arm. Participants randomised to the control arm will continue sunitinib according to the CCS i.e. continuing treatment until evidence of disease progression or toxicity precluding continuation. Participants randomised to the experimental arm will continue according to the DFIS i.e. they will temporarily stop sunitinib (a planned treatment break). Participants will remain off treatment until radiologically-confirmed evidence of disease progression. At this time sunitinib will be restarted following the same scheduling and dose as before. In participants who regain further disease control, after completion of a minimum of 4 cycles of sunitinib and maximal radiological response, further planned treatment breaks will be implemented.

All participants will continue with their allocated sunitinib treatment strategy as per protocol (with dose reductions as required) until radiologically-confirmed disease progression occurs whilst taking sunitinib, unacceptable toxicity or participant choice to stop per protocol treatment

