### Follow-up

The planned duration of the trial follow-up is until 2 years after the last participant is randomised. During continuation of protocol-defined treatment (sunitinib as per CCS or DFIS) six-weekly clinical assessments and twelve-weekly radiological assessments will occur, in line with standard practice. Where protocol-defined treatment has permanently stopped, details of any subsequent treatment received for renal cancer and the participant’s status will be collected at six months and then on an annual basis.

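### SPFI counts the delay until a 12-weekly scan shows progression as progression-free time once per counted treatment block, which favours DFIS over CCS if true progression-free time is equal

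*Protocol article*

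**What the plan says.** Endnote b gives the definition: SPFI "is defined as the sum of the intervals from the start of each treatment block with sunitinib, until radiological evidence of disease progression". It adds a condition: "provided there has been some evidence of disease control prior to ongoing progression". A block that brings no disease control therefore adds no interval.

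The scan schedule is in the Follow-up section: "During continuation of protocol-defined treatment (sunitinib as per CCS or DFIS) six-weekly clinical assessments and twelve-weekly radiological assessments will occur". It is the same for both strategies and covers treatment breaks.

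The Intervention section says when a DFIS break ends: "Participants will remain off treatment until radiologically-confirmed evidence of disease progression. At this time sunitinib will be restarted". Further breaks can follow if control is regained. CCS is one continuous block of sunitinib.

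SPFI is the first of six bulleted items under Secondary objectives. No margin, power or decision rule is attached to it. The Stage B decision rests on TSF, and the co-primary endpoints are OS and averaged QALY.

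**The concern.** In an ordinary comparison of PFS on equal scan schedules, both arms carry one detection lag and it largely cancels. SPFI is different because the number of scan-dated endpoints differs between the arms by design. In DFIS the first interval runs through the break to the scan that shows progression. The time between true progression and that scan is credited as progression-free, and a new interval then starts at the restart. CCS has one such credit, and DFIS has one per counted block.

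The article says PFS is not a suitable comparator because of the breaks, and in its Background it cites comparable summative PFS under intermittent sorafenib as ethical support for the design. A summed measure of this kind is therefore likely to be read as evidence on whether breaks preserve disease control. If part of it is scan rounding that favours the experimental strategy, an equal or longer SPFI in DFIS could hide a real loss.

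**Working it through.** The article gives no figure of its own for SPFI, so there is nothing to reproduce. The check is the size of the lag and how it accumulates.

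**Inputs**
- Scan interval D = 12 weeks (Follow-up).
- First-line sunitinib: median PFS 11 months, or 47.8 weeks (Background). Hazard λ = ln 2 / 47.8 = 0.0145 per week.
- Sunitinib re-challenge: median 7.2 months, or 31.3 weeks (Intermittent anti-cancer treatment strategies). λ = 0.0221.
- Randomised sorafenib study, same section: "At 24 weeks 50% of patients continuing sorafenib were progression-free compared with 18% of placebo-treated patients". Randomisation was at 12 weeks, so these are proportions 12 weeks later. λ = -ln(0.18)/12 = 0.143 off drug; λ = -ln(0.50)/12 = 0.058 if continued.
- Share taking up the strategy at 6 months: 53% (Stage B; 112 of 210).

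**Mean lag per interval.** If progression is uniform between scans, the lag is D/2 = 6.0 weeks. If it is exponential, the lag is D/(1 - exp(-λD)) - 1/λ:
- 11-month median: 6.2 weeks.
- 7.2-month median: 6.3 weeks.
- Median 26 weeks on a break (assumed): 6.3 weeks.
- 50% progression-free at 12 weeks, the same as a 12-week median: 12/0.50 - 17.3 = 6.7 weeks.
- 18% progression-free at 12 weeks off drug: 12/0.82 - 7.0 = 7.6 weeks.

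**Accumulation.** A simulation of 400,000 participants gave both arms identical summed true progression-free time. CCS had one interval rounded up to the next 12-week scan, and DFIS had two or three intervals, each rounded up. The first DFIS interval was 24 weeks on drug plus an exponential time off drug, at the 18% or the 50% rate. The last used the 7.2-month re-challenge hazard.
- One extra counted block: mean SPFI longer in DFIS by 6.9 weeks (50% rate) to 7.9 weeks (18% rate); ratio of means 1.08 to 1.10.
- Two extra counted blocks: longer by 13.6 to 15.6 weeks; ratio 1.10 to 1.14.
- Medians, which move in 12-week steps here, differed by 0 weeks with one extra block and by 12 to 24 weeks with two. The weekly figures therefore describe means.

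**Arm average.** With one extra counted block in each of the 53%: 0.53 × 6.0 = 3.2 weeks, 0.53 × 6.7 = 3.6 weeks, 0.53 × 7.6 = 4.0 weeks.

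**With midpoint dating.** Each interval ends 6 weeks earlier, so the residual per interval is the lag minus 6: 0 weeks if uniform, 0.2 to 0.7 weeks at the slower rates, and 1.6 weeks at the 18% rate.

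**Sensitivity to visits.** If every progression were picked up at a 6-weekly clinic visit, the lag would be about 3.0 to 3.4 weeks. The article does not provide for scans triggered this way.

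**The case against.** The strongest objection is that the sum telescopes. Sunitinib restarts when progression is confirmed, so one interval ends about where the next begins. SPFI is then roughly the time from first dose to the last counted progression. If the arms have equal true time to final progression on drug, each has one terminal overshoot and SPFI does not differ. On this view the intermediate lags lengthen SPFI only if late detection does not shorten the next block, and the article gives no figure on that. This stands as a limit: the excess is conditional on equal summed true progression-free time. It does not dispose of the point, because time to final failure is what TSF measures. SPFI is named as progression-free time, and for that quantity the rule still credits undetected progression more often in DFIS.

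A reader might infer more than the documents support:
- That every extra block adds 6-8 weeks. Endnote b excludes blocks without disease control. A DFIS participant who never regains control has one interval, and differs from CCS by about 0.1 to 1.4 weeks (6.3 - 6.2 to 7.6 - 6.2).
- That the bias is 13-16% of the 11-month median PFS (6.3/47.8 to 7.6/47.8). This sets a lag in participants with an extra counted block against a whole-population median.
- That the 18% figure is typical of STAR breaks. It comes from another drug, in patients with stable disease after 12 weeks. STAR breaks follow at least four cycles and maximal response. A small, selected series of 11 complete responders cited in the article had 5 recurrences at a median follow-up of 8.5 months, which suggests slower progression off drug. Slower progression moves the lag towards 6 weeks, not towards zero.
- That SPFI is the trial's test of preserved disease control. No section gives it that role.

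It can also be said that dating conventions belong in the SAP, which the article promises. That is fair as to detail, and the SAP may already deal with it. But the article itself fixes the end of each interval at radiological evidence, and that stated rule creates the asymmetry.

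**Conclusion.** The point holds in a limited form. As defined, SPFI credits undetected progression once per counted block, so the credit falls more often on DFIS than on CCS. If summed true progression-free time were equal, mean SPFI would be longer in DFIS by roughly 6-8 weeks per extra counted block, or about 3-4 weeks as an arm average under the 53% scenario.

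This rests on uniform or exponential progression between scans, no unscheduled scans, and no shortening of the next block by late detection. The direction does not depend on the sorafenib figure, since uniform progression still gives 6 weeks. The consequence is confined to how one secondary endpoint is read. The Stage B decision and the OS and QALY conclusions are untouched.

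**What to change.** In both arms, add an SPFI analysis in which each interval ends at the midpoint between the last scan without progression and the first scan showing it, or in which each interval is treated as interval-censored. Report it beside the scan-date version. State in advance that an equal or longer scan-date SPFI in DFIS will not be read as preserved disease control unless the midpoint version agrees.

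The cost is wording and one further analysis. It uses the dates of scans already scheduled and changes no visit, scan or treatment.

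There is a downside to state. Midpoint dating departs from the scan-date convention, and it takes about 6 weeks off each interval: about 6 weeks from a CCS participant, and about 12 from a DFIS participant with two counted blocks. If the arms have equal time to final progression, this works against DFIS. That is why both versions should be shown.
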